### Data collection

Figure 1 shows all participant data collection at time points outlined below and indicates how intervention delivery fits with this. Figure 2 is a study flow diagram.

**Figure 1 F1:**
[figure not shown]
Schedule of data collection and intervention delivery time points. ^a^Participants who accepted component 3 of the intervention—Reduction. ^b^CO reading collected directly during face-to-face appointment or from a recent antenatal appointment record. ^c^Intervention group only, until approximately 30 paired samples obtained. ^d^Validation sample, only collected from participants who reported not smoking in the last 7 days. ^e^Intervention group only. CO, carbon monoxide; NRT, nicotine replacement therapy; SSS, Stop Smoking Services.

**Figure 2 F2:**
[figure not shown]
Study flow diagram. CO, carbon monoxide; cpd, cigarettes per day; NRT, nicotine replacement therapy; PIS, patient information sheet;

#### Baseline

Researchers will collect the following baseline data: socio-demographics; smoking beliefs and behaviours; gestation; nicotine dependence^32^; urges to smoke; number of births beyond 24 weeks and significant others’ smoking status. Those recruited in person will be asked to provide an expired air CO reading, and for those recruited remotely we will seek a recent CO reading from antenatal appointment records. For those in the intervention group, we will ask them to provide a saliva sample. For participants recruited remotely, we will post out self-collection saliva sample kits, and samples will be posted directly to the study laboratory for cotinine measurement. (Please note, identical sample collection procedures will be used at all time points).

#### Follow-up

Where possible, data will be first sought via online questionnaires, and if unsuccessful, by telephone, email, text or postal questionnaire. Data collection will occur:

7 days after preloading starts (intervention group only).6 weeks after randomisation.8–12 weeks after randomisation (for those who accept the NRT for smoking reduction intervention only).At 36 weeks gestation (or childbirth, if earlier).After childbirth.

#### Day 7 of preloading intervention

We will ask intervention group participants how many daily cigarettes they smoke, about use of preloading NRT and for a saliva sample; baseline and day 7 saliva sample collection will end when we have around 30 paired samples.

#### Randomisation plus 6 weeks

We will ask about smoking status, quitting behaviour, use of preloading NRT, whether a QD was set and use of non-study stop smoking support. For those who report a quit attempt, we will ask if they used NRT for quitting, and if any smoking lapse(s) occurred, whether NRT was continued or stopped. To prevent researchers’ becoming aware of participants’ treatment allocations, which could bias questioning about smoking, questions about smoking will be asked at the very outset, before questions about treatments.

#### Offering NRT for smoking reduction

We will aim to offer the third intervention component to all intervention group participants who are smoking and not interested in trying to quit. Hence, if follow-up is by telephone, we will offer this during the call; alternatively, we will contact those participants who report smoking in their responses to online questionnaires. Those who accept NRT for help with smoking reduction, and for whom there is no baseline saliva sample, will be asked to provide one before they start using NRT for reduction.

#### 8–12 weeks postrandomisation

We will ask those who accepted NRT for smoking reduction how many daily cigarettes they smoke, about use of preloading NRT, and to provide a saliva sample and an exhaled air CO sample.

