##### Birth and maternal outcomes

We will seek maternal and fetal pregnancy outcome data, and information on infant gender, birth weight, gestation at delivery, mode of delivery, admission to neonatal intensive care, congenital anomalies or neonatal death. *Smoking outcomes*: We will seek smoking status and CO readings recorded in electronic medical records at 36 weeks, the time of delivery and from any clinic appointments occurring close to study enrolment.

Where birth and late pregnancy smoking data are still missing after this final attempt at data collection, we will seek them directly from participants via text message or telephone.

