#### Exploratory outcomes

Exhaled CO and cigarettes smoked per day when using NRT for ‘preloading’ or to cut down smokingSaliva cotinine concentration when using NRT for ‘preloading’ or to cut down smokingUse of stop smoking support

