#### Exploratory outcomes

We intend to use paired saliva samples to estimate participants’ cotinine concentrations when (1) smoking at baseline and using NRT for (2) preloading and (3) smoking reduction.

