Further exploratory analyses will be carried out for women in the intervention arm who are offered NRT for (1) preloading and (2) smoking reduction; these will describe saliva cotinine and exhaled CO concentrations when smoking with those when (1) preloading and (2) using NRT to reduce smoking. Previous studies suggested that it would be reasonable to collect 30 paired samples for this analysis.^37^ Another exploratory analysis will describe and compare the characteristics and outcomes of women who accept and do not accept NRT for smoking reduction and cessation induction. This will be the first study of pregnant women to be offered NRT for smoking reduction as part of a trial.

Full details of analyses will be provided in a statistical analysis plan (SAP), which will be finalised and approved prior to the database lock and before the trial statisticians are unblinded. This will then be added to the ISRCTN registry.

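### The data collection text does not match the exploratory NRT-exposure analyses: it asks about the wrong NRT use at 8–12 weeks, lists no CO at day 7 of preloading, and does not ask about NRT use with late baseline saliva

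*Protocol article*

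**What the plan says.** Two exploratory outcomes concern women using NRT while they still smoke. One is "Exhaled CO and cigarettes smoked per day when using NRT for" preloading or cutting down; the other is saliva cotinine in the same two situations (Exploratory outcomes, under Secondary outcomes). A second passage with that heading, under Sample size and justification, says "We intend to use paired saliva samples to estimate participants’ cotinine concentrations when (1) smoking at baseline and using NRT for (2) preloading" and, as a third state, smoking reduction. Of the planned summaries, the Analyses section says "these will describe saliva cotinine and exhaled CO concentrations when smoking with those when (1) preloading and (2) using NRT to reduce smoking".

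The collection text reads as follows:

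- **Baseline.** In-person recruits are asked for a CO reading; "for those recruited remotely we will seek a recent CO reading from antenatal appointment records". Saliva is requested from the intervention group.
- **Day 7 of preloading.** Women are asked "how many daily cigarettes they smoke, about use of preloading NRT and for a saliva sample". Baseline and day 7 saliva collection stops at around 30 pairs.
- **Before reduction NRT.** Women who accept it and "for whom there is no baseline saliva sample, will be asked to provide one before they start using NRT for reduction".
- **8–12 weeks, reduction acceptors only.** Women are asked "how many daily cigarettes they smoke, about use of preloading NRT, and to provide a saliva sample and an exhaled air CO sample".
- **After childbirth.** Staff seek "CO readings recorded in electronic medical records at 36 weeks, the time of delivery and from any clinic appointments occurring close to study enrolment".

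**The concern.** An exposure comparison needs the measurement in each state and proof that the woman was in that state when measured. The text falls short in three places.

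First, the 8–12 week contact asks about preloading NRT in a group defined by having accepted reduction NRT. Second, CO during preloading is named as an outcome, but the text of the one contact tied to preloading does not list it. Third, the reference state is smoking at baseline, yet some reference samples will be taken around week 6, after NRT has been offered for preloading and for use during lapses.

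Saliva at 36 weeks is sought only from women reporting abstinence, so the day 7 and 8–12 week samples are the only listed saliva collections from women who may be smoking while on NRT. If NRT status at those samples is unknown, a change, or the lack of one, is hard to interpret.

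**Working it through.** The article calculates no figure for these analyses, so the check sets each need against the collection text.

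| State | CO | Cotinine | NRT use at sampling |
|---|---|---|---|
| Smoking (reference), enrolment sample | listed, measured or from records | listed | before study NRT |
| Smoking (reference), pre-reduction sample | as above | listed | not listed |
| Preloading, day 7 | **not in text** | listed | listed |
| Reduction, 8–12 weeks | listed | listed | **preloading NRT named instead** |

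**8–12 week item.** Component 1 gives patches for 1–4 weeks before the quit date. To be preloading still at week 8, a woman would have to start at week 8 − 4 = 4 or later. For anyone who starts earlier, the question concerns a finished exposure. The item repeats the day 7 wording and looks carried over. Accepting reduction NRT does not show that it is being used: Component 3 makes supply contingent on sufficient reduction, and the Patient and public involvement section says provision stops if smoking is heavy enough. If a fraction f of those sampled are off NRT, the observed mean change is (1 − f) × (change on NRT) + f × (change off NRT). The article gives no value for f or for either change, so the effect has no computable size.

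**CO in preloading.** Baseline CO precedes study NRT. Record-based CO is tied to 36 weeks, delivery and appointments near enrolment. A near-enrolment reading could fall within preloading by chance, but nothing links it to patch use. The text names CO at 8–12 weeks and not at day 7, so the omission is specific.

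**Late reference saliva.** Reduction is offered at week 6. A four-week preload begun at week 6 − 4 = 2 or later would still be running then, and Component 2 advises continuing NRT through brief lapses. The pre-reduction sample is required to precede reduction NRT only, not other NRT. Any NRT nicotine in it raises the reference, so a rise on reduction NRT would be understated by that amount. At 36 weeks, by contrast, the article does ask about recent NRT or e-cigarette use before saliva is taken.

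**Why NRT status matters.** In the earlier patch trial cited in the Introduction, cotinine was similar when smoking and when smoking with a patch: 118 and 111 ng/mL, 111/118 = 0.94 (95% CI 0.83 to 1.07). Similar cotinine can mean that NRT replaced tobacco nicotine, or that NRT was not used and smoking did not change. Only cigarettes and current NRT use, recorded together, separate the two.

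**The case against.** The strongest reply is that this is a condensed article. Figure 1 is said to show all participant data collection and is not available here. One of its footnotes describes CO taken face to face or from antenatal records, so a day 7 CO entry cannot be excluded. That stands: a reader might infer that no CO reading is planned during preloading, and the text alone does not prove it.

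A reader might also infer that cotinine data are missing, or that nothing is measured in the reduction phase. The text contradicts both: saliva is listed in every phase and CO at 8–12 weeks.

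On NRT use, Component 3 includes the MyNRT app for self-monitoring, biweekly counselling and two-week supplies, and the week 6 contact asks about preloading NRT, NRT for quitting and NRT in lapses. Component 2 also advises stopping NRT when lapses persist, so many women still smoking at week 6 may be off it. This reduces the problem without removing it. App entries are voluntary self-monitoring and not tied to the sample; supply is not use; and the week 6 questions are not stated to cover current use on the day of the saliva sample.

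Finally, the figure of around 30 pairs is attached to baseline and day 7 samples. A reader might take it as the size of the reduction comparison, but the article does not clearly say so.

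**Conclusion.** The mismatch between text and analysis is real and small. The 8–12 week item names the wrong exposure. The day 7 text omits CO that the outcomes and analysis sections name. Late reference saliva may be given on other NRT with no listed check. The first and third points rest on the prose describing the questionnaires accurately; the second is conditional on Figure 1.

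It would go too far to say that the comparisons have no data, or to put a percentage on the dilution of the reduction contrast: the article gives no rate of non-use. The analyses affected are exploratory and descriptive, within the intervention arm. The primary outcome, the sample size and the randomised comparison are untouched. This is a worthwhile tidy-up, not a threat to the trial.

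**What to change.** 1. In 8–12 weeks postrandomisation, replace the item on preloading NRT with one on current use of NRT for reduction at the time of sampling: product, amount and last use.
2. In Offering NRT for smoking reduction, ask about current NRT use with every pre-reduction reference saliva sample. Flag samples given while on NRT, or analyse them separately from those given when smoking alone.
3. If Figure 1 schedules CO at day 7, add it to the day 7 text. If not, drop CO from the preloading comparison in Exploratory outcomes and Analyses, and keep cotinine and cigarettes per day.

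The cost is one reworded item, one added item and a line in the SAP, with slightly fewer clean pairs. By 30 September 2025, 930 of 1430 participants (65%) had been enrolled, so new questions reach only samples still to be taken. For earlier samples, classify NRT status from week 6 answers and app records where these allow, and report the rest as unknown.

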#### 36 weeks gestation (or childbirth, if earlier)

We will ask about smoking behaviours and quit attempts, NRT and e-cigarette use, use of stop smoking support and about relevant cost data. We will attempt to collect saliva samples from all who report abstinence from smoking for at least 7 days. Samples will be requested postally (see above) or at hospital attendance and before collection we will ask, by questionnaire or verbally, about smoking and recent use of NRT or e-cigarettes.

#### After childbirth

Most data collection at this point will involve hospital staff extracting data from participants’ medical records.

##### Birth and maternal outcomes

We will seek maternal and fetal pregnancy outcome data, and information on infant gender, birth weight, gestation at delivery, mode of delivery, admission to neonatal intensive care, congenital anomalies or neonatal death. *Smoking outcomes*: We will seek smoking status and CO readings recorded in electronic medical records at 36 weeks, the time of delivery and from any clinic appointments occurring close to study enrolment.

Where birth and late pregnancy smoking data are still missing after this final attempt at data collection, we will seek them directly from participants via text message or telephone.

##### Incentives for follow-up completion

Participants will be offered £5 high street shopping vouchers for returning completed follow-up questionnaires, and a £20 voucher for providing validation saliva samples at 36 weeks.

### Qualitative substudy to optimise recruitment

Early in the trial, we will interview up to 28 women who are offered trial enrolment. We will aim to include approximately 10 participants from each arm and up to eight who decline participation. We will design and pilot interview guides for participants and non-participants and interview them, asking about acceptability of being offered participation, perceived barriers against and facilitators for joining the study, and whether approaches to potential participants could be improved. Participants will also be asked about acceptability of and concerns about intervention components. Interviews will be recorded and transcribed, and interviewees will be offered a £20 shopping voucher as compensation for their time. There will be a pragmatic, thematic analysis, with findings hopefully informing study modifications that will enhance recruitment.

### Data management and archiving

Participants will be assigned unique study identification numbers used to identify their data and biological samples. Identifiable data, such as name/date of birth/contact details, will be stored in a password-protected database accessible only by the research team. If a paper case report form (CRF) is used, data will be entered by researchers onto the database and the paper CRF will be stored in a secure location in the investigator site file. Information submitted by participants via the MyNRT app will be stored as pseudonymised data on Amazon cloud.

Data Management is led by Nottingham Clinical Trials Unit, with the support of the Trial Manager in the University of Nottingham as detailed in the Data Management Plan.

The Trial Management Group will be responsible for the day-to-day running of the trial, meeting on a regular basis and will be supported by, and report to, the Trial Steering Committee (TSC) and the Data Management Committee (DMC).

Saliva samples will be analysed at the end of the trial by ACM Biomedical Services, an external laboratory to quantify salivary cotinine concentrations and the presence or absence of anabasine using a quantitative enzyme immunoassay technique. After analysis, samples will be destroyed in accordance with the Human Tissue Act 2004.

In compliance with the The Global Health Network’s International Council for Harmonisation (ICH) Good Clinical Practice (GCP) guidelines/regulations and in accordance with the University of Nottingham Research Code of Conduct and Research Ethics, the chief or local principal investigator will maintain all records and documents regarding the conduct of the study. These will be retained for at least 7 years following the end of study data lock or for longer if required. If the responsible investigator is no longer able to maintain the study records, a second person will be nominated to take over this responsibility.

The trial master file and trial documents held by the chief investigator on behalf of the sponsor shall be finally archived at secure archive facilities at the University of Nottingham. This archive shall include all trial databases and associated meta-data encryption codes.

## Outcomes

### Primary outcome

Biochemically validated, prolonged abstinence from smoking reported between 6 weeks after randomisation and 36 weeks gestation or childbirth, whichever is earlier.

Smoking lapses are permitted during this period, provided no more than five cigarettes in total are smoked and a 7-day period of total abstinence is reported immediately before primary outcome follow-up.

### Secondary outcomes

#### Smoking-related

Reported and validated 7-day smoking abstinence at 36 weeks gestationReported ≥50% reduction in daily cigarettes at 36 weeks gestationExhaled CO concentration at deliveryBrief smoking lapse(s) reported at 6 weeks postrandomisation

#### Pregnancy and safety-related

MiscarriageStillbirthLBW for gestational ageUnadjusted birth weight and birth weight z scorePremature birthGestation at birthCongenital abnormalityMode of deliveryAdmission to special careNeonatal death

#### Exploratory outcomes

Exhaled CO and cigarettes smoked per day when using NRT for ‘preloading’ or to cut down smokingSaliva cotinine concentration when using NRT for ‘preloading’ or to cut down smokingUse of stop smoking support

### Sample size and justification

To detect a difference in smoking cessation in late pregnancy between control and intervention group proportions of 0.1 and 0.159, respectively, (OR of 1.70) with 90% power and 5% two-sided alpha requires 715 participants per arm (total n=1430). There is no adjustment for missing data; it will be assumed those lost to follow-up are smoking. Based on a recent SiP trial,^33^ assuming a quit rate in the UC group of 10% and anticipating an OR of 1.70 for the effects of NRT (1) as preloading and (2) continued in smoking lapses to facilitate return to abstinence. An OR of 1.7 is considered clinically important and plausible, based on the anticipated effect of *preloading*^17 34^ and *lapse prevention*^21 35 36^ intervention components. The third intervention component (*NRT for smoking reduction*) will not contribute to the primary outcome as this is offered to participants who have returned to smoking.

#### Exploratory outcomes

We intend to use paired saliva samples to estimate participants’ cotinine concentrations when (1) smoking at baseline and using NRT for (2) preloading and (3) smoking reduction.

## Analyses

Descriptive statistics of demographic and clinical measures will be used to assess balance between the randomised arms at baseline, but no formal statistical comparisons will be made. Continuous variables will be summarised in terms of the mean, SD, median, lower and upper quartiles, minimum, maximum and number of observations. Categorical variables will be summarised in terms of frequency counts and percentages.

The primary between-group analysis will use the intention-to-treat population, with those lost to follow-up considered to be smoking. The primary outcome will be analysed using a mixed-effect logistic regression model adjusted for randomisation stratification variables with a random effect for site. The estimate between-group effect will be presented using both absolute and relative measures of effect, with associated 95% CIs.

Maternal secondary outcomes will be analysed similarly, using appropriate regression models depending on the type of outcome variable and adjusting for randomisation stratification variables. Infant secondary outcomes will be analysed using appropriate regression models depending on the type of outcome variable, adjusting for randomisation stratification variables and accounting for correlation between outcomes for infants from multiple pregnancies.

Primary analysis will be repeated additionally, adjusting for any variables with marked imbalance at baseline.

Using appropriate interaction terms in the primary regression analyses for prolonged smoking cessation, it will be investigated whether treatment effectiveness differs according to the baseline level of nicotine dependence. Since the trial is powered to detect overall differences between the groups rather than interactions of this kind, this subgroup analysis will be regarded as exploratory.

Further exploratory analyses will be carried out for women in the intervention arm who are offered NRT for (1) preloading and (2) smoking reduction; these will describe saliva cotinine and exhaled CO concentrations when smoking with those when (1) preloading and (2) using NRT to reduce smoking. Previous studies suggested that it would be reasonable to collect 30 paired samples for this analysis.^37^ Another exploratory analysis will describe and compare the characteristics and outcomes of women who accept and do not accept NRT for smoking reduction and cessation induction. This will be the first study of pregnant women to be offered NRT for smoking reduction as part of a trial.

Full details of analyses will be provided in a statistical analysis plan (SAP), which will be finalised and approved prior to the database lock and before the trial statisticians are unblinded. This will then be added to the ISRCTN registry.

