### Randomisation and blinding

Once informed consent is documented, the researcher will collect baseline data, before randomising the participant to either the intervention or control group in a 1:1 ratio, using the Nottingham Clinical Trials Unit’s web-based randomisation system. The randomisation schedule is stratified by site and level of nicotine addiction and is based on a computer-generated pseudo-random code using random permuted blocks of varying size.

Participants will be aware of their treatment allocation, but researchers who collect primary outcome data will be blinded. Staff randomising participants will not be blinded to treatment allocation, as they will need to ensure participants in each group receive relevant treatment information and referral, if required.

The trial statistician will remain blinded prior to database lock and will be unblinded prior to conducting the final analysis.

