### Procedures for missing, unused and spurious data

For the primary analysis of the primary outcome and for other smoking-related secondary outcomes, participants with missing data will be considered to still be smoking; this is consistent with Russell Criteria, which defines standard smoking cessation study outcomes^38^ and has been proven a rational assumption in similar contexts.^39^ However, sensitivity analyses (described in detail in the SAP) will be conducted, which make different assumptions to investigate the potential impact of missing smoking abstinence data.

Analyses of other secondary outcomes will use available data, that is, with no imputation for participants with missing data.

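### Exhaled CO at delivery could also be adjusted for baseline CO, a modest and free gain in precision on one secondary outcome

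*Protocol article*

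**What the plan says.** In the protocol article, the Analyses section states one covariate set for all maternal secondary outcomes: they are modelled "using appropriate regression models depending on the type of outcome variable and adjusting for randomisation stratification variables". Randomisation and blinding identifies those variables: "The randomisation schedule is stratified by site and level of nicotine addiction". Exhaled CO at delivery is listed among the smoking-related secondary outcomes and is named in the secondary objectives, so it falls under this sentence.

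Three CO readings are mentioned:

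- **Baseline.** "Those recruited in person will be asked to provide an expired air CO reading", whereas "for those recruited remotely we will seek a recent CO reading from antenatal appointment records". The section on birth and maternal outcomes adds that readings from clinic visits near enrolment will be sought after childbirth.
- **36 weeks and delivery.** "We will seek smoking status and CO readings recorded in electronic medical records at 36 weeks, the time of delivery".

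The one further adjustment in the Analyses section is triggered by imbalance and confined to the primary analysis: "Primary analysis will be repeated additionally, adjusting for any variables with marked imbalance at baseline". Full analytic detail is deferred to an SAP that is not shown.

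**The concern.** Exhaled CO at delivery is the only continuous, objective smoking outcome compared between the arms. The other smoking-related secondary outcomes are abstinence, reported reduction and reported lapses, and the exploratory CO and cotinine analyses concern the intervention arm. The sample size section says that the third component, NRT for smoking reduction, will not contribute to the primary outcome. Among the smoking measures, its effect would therefore show mainly in reported reduction, in a trial where women know their allocation, or in CO at delivery.

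If women with high CO at enrolment also tend to have high CO at delivery, that spread stays in the residual unless baseline CO is in the model. What is at stake is the width of one interval. Validity is not in question.

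**Working it through.** **1. The plan's own figures.** The article gives no standard deviation, power or sample size for CO. Its only sample size is for the binary primary outcome. With a control rate of 0.10 and an odds ratio of 1.70, the odds are 1.70 × 0.10/0.90 = 0.1889, so the intervention rate is 0.1889/1.1889 = 0.1589. The two-proportion formula with continuity correction, two-sided 5% alpha and 90% power, gives 715 per arm, or 1430, as stated. CO does not enter this calculation.

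**2. Gain from baseline CO alone.** Let r be the correlation between baseline and delivery CO, and f the share of women with a baseline reading. The documents give neither, so both are assumptions. The approximate variance ratio, adjusted to unadjusted, is 1 − f·r², and the standard error (SE) ratio is its square root.

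| r | Variance ratio, f = 1 | SE ratio, f = 1 | Variance ratio, f = 0.5 | SE ratio, f = 0.5 |
|---|---|---|---|---|
| 0.3 | 0.91 | 0.954 | 0.955 | 0.977 |
| 0.4 | 0.84 | 0.917 | 0.92 | 0.959 |
| 0.5 | 0.75 | 0.866 | 0.875 | 0.935 |
| 0.6 | 0.64 | 0.800 | 0.82 | 0.906 |

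With complete baseline readings the variance falls by 9% to 36%, equivalent to 1/0.91 = 1.10 to 1/0.64 = 1.56 times as many women. With half measured it falls by 4.5% to 18%.

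**3. Allowing for dependence already in the model.** Let s be the correlation of dependence level with delivery CO and q its correlation with baseline CO, both assumed. Then R² = (r² + s² − 2rsq)/(1 − q²), and the net variance ratio is (1 − R²)/(1 − s²). Take r = 0.5, s = 0.3 and q = 0.4:

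- R² = (0.25 + 0.09 − 0.12)/0.84 = 0.262
- net ratio = 0.738/0.91 = 0.811, against 0.75 in step 2

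| r (q = 0.4, f = 1) | s = 0.3 | s = 0.4 |
|---|---|---|
| 0.3 | 0.958 | 0.972 |
| 0.5 | 0.811 | 0.836 |
| 0.6 | 0.699 | 0.726 |

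If only half the women have a baseline reading, the reduction is roughly halved. At r = 0.3 and s = 0.4 it is 0.5 × (1 − 0.972) = 1.4%. At r = 0.6 and s = 0.3 it is 0.5 × (1 − 0.699) = 15%.

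**4. Why the 36-week reading must not be a covariate.** It is taken after randomisation, so treatment can affect it. In 1000 simulated trials of 1430 women, the true effect was −0.20 SD at both 36 weeks and delivery, and baseline CO correlated 0.5 with each later reading. Adjusting for baseline CO left the mean estimate at about −0.20 and cut the SE from 0.053 to 0.046. Adding 36-week CO gave:

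| Correlation, 36 weeks to delivery | Mean estimate | SE |
|---|---|---|
| 0.5 | −0.131 | 0.044 |
| 0.7 | −0.080 | 0.037 |
| 0.8 | −0.055 | 0.031 |

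Algebra agrees. The coefficient of 36-week CO given baseline is (ρ − 0.25)/0.75, where ρ is the correlation in the first column. At ρ = 0.7 it is 0.6, leaving −0.20 × 0.4 = −0.08. The smaller SE belongs to a different quantity, from which one third to about three quarters of the effect has been removed.

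**The case against.** The strongest objection is that one summary sentence in a condensed article does not settle the covariates for every outcome. It does not say that the stratification variables are the only ones, and the SAP may well add baseline CO. This stands in part. The point is no error, and it may already be met. But the article does state a covariate set, and the only extension it describes is for the primary analysis, so the improvement is to a stated method.

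A reader might go further in three ways that the documents do not support.

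- **That every woman's baseline and 36-week CO is in hand.** Remote recruits' baseline readings, and all the 36-week and delivery readings described for extraction, depend on routine records. Coverage is unknown, so the figures for complete baseline readings are upper limits.
- **That the model should also adjust for 36-week CO, or that this reading is wasted.** As a covariate it would remove part of the effect. Nor does the article say that it is discarded: exhaled CO is among the measures listed for validating reported abstinence.
- **That a joint model of 36-week and delivery CO is equally free.** It would assume that readings are missing at random, whereas the stated rule is that "for other smoking-related secondary outcomes, participants with missing data will be considered to still be smoking". That rule supplies no CO value for a continuous outcome, but replacing it is a trade-off.

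**Conclusion.** The point holds as an optional efficiency improvement to one secondary outcome. For an assumed baseline-to-delivery correlation of 0.3 to 0.6, the variance reduction is at most 9% to 36%. It is about half that if half the women have a baseline reading. Once dependence level is counted as well, under the correlations assumed above, it is about 1% to 15%. None of these inputs can be checked from the documents.

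A reader might infer that the planned CO analysis is biased or wrong. It is not: under randomisation, omitting a prognostic baseline covariate from a linear model costs precision and does not bias the arm difference. The primary analysis and the sample size do not change.

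**What to change.** State in the SAP, or confirm if it is already there, that for exhaled CO at delivery:

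- the model includes baseline exhaled CO, for example on the log scale, in addition to the stratification variables;
- women without a baseline reading are kept, by a missing indicator or mean imputation;
- a reading counts as baseline only if it was taken before randomisation. This needs saying because record readings are described as close to enrolment, and CO monitoring is also part of the advice given after randomisation;
- no CO reading taken after randomisation, including the 36-week one, is a covariate. At most, the 36-week reading serves as a repeated outcome or auxiliary variable in a sensitivity analysis.

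The cost is a few lines of SAP text and no new data collection. The article has the SAP finalised before database lock and unblinding, and expects the last participant visit in April 2027, so on that timetable the wording can be settled in time.
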